### **17.3 Blinding and Unblinding**

The study monitor, the investigator(s), and the subjects at the site will be blinded to treatment assignment. The unblinded third party pharmacist will not participate in the evaluation of any study subject. This will permit all other participants to remain blinded. The unblinded third party pharmacist will prepare and label all treatments with the names and randomization numbers of the subjects based on the randomization list. Individuals who are unaware of the test article random assignment will administer the treatments to the subjects. Contact between the unblinded third party pharmacist and study subjects will be kept to a minimum. The investigator, sub-investigator, research nurse, and any study participants other than the unblinded third party pharmacist will not be allowed to know the treatment assigned to any study subject and will not have access to the randomization treatment records.

The subject's treatment will be unblinded electively only if an AE occurs that the investigator, the Wyeth medical monitor and the WHO clinical coordinator or project manager believe requires identification of the treatment assignment. This may occur in the case of a SAE, as the investigator's decision to enroll the next cohort within the same dose group may be influenced by whether a SAE occurred in a subject or subjects who received moxidectin or in one who received ivermectin. This will also affect the sponsors' agreement with the investigator's decision. In this case, the unblinded third party pharmacist will inform the investigator, who will inform the Wyeth medical monitor of the subject's treatment assignment and the reason(s) for breaking the randomization code.

Routine unblinding of SAEs will not be performed in this protocol. Ivermectin and moxidectin are macrocyclic lactones and are expected to have similar adverse event profiles. This is a single-dose study and thus there will be no question regarding continuation of therapy after an SAE. The treatment of SAEs will not be affected by whether the subject receives ivermectin or moxidectin.

Emergency unblinding will be at the discretion of the Principal Investigator. The investigator must submit a written explanation describing the event to the sponsors within 5 working days. All randomization envelopes must be returned to the sponsors at the completion of the trial.

## **18. SAFETY**

### **18.1 Safety Variables**

All subjects enrolled in this study will be closely monitored for safety and evaluated for any AEs. Safety evaluation will include: symptoms, physical examinations, vital signs measurement, ECGs, ocular exams, and laboratory evaluations. All evaluations will be monitored as outlined in section 16.1, Procedures, and section 16.3, Special Methods. A key safety component of the study drug will be determined by the presence and severity of the Mazzotti reaction. An important consideration in the administration of microfilaricides to *O. volvulus* infected subjects is the potential for the combination of AEs due to the pharmacologic properties of the drug with the constellation of symptoms, signs and laboratory events that occur when microfilariae are killed (the Mazzotti reaction). These need to be differentiated one from the other and from any coincidental illnesses that may occur in temporal relationship with test drug administration. Common systemic clinical manifestations of the Mazzotti reaction include pruritus, rash, lymphadenitis, headache, myalgia, arthralgia, hypotension, fever and swellings of the face and limbs. Ocular events include epiphora, photophobia, conjunctival injection, limbitis, anterior uveitis, chorioretinitis and optic neuritis.

The clinical laboratory changes involve the peripheral blood leucocytes, aspartate aminotransferase (AST/SGOT) and alanine aminotransferase (ALT/SGPT) and sometimes lactate dehydrogenase (LDH) and gamma-glutamyl-transferase (GGT); microfilariae also appear in blood, urine, and other body fluids. The eosinophils exhibit the most prominent changes. There may be an initial eosinopenia followed several days later by a marked increase above pretreatment levels. A complete disappearance of eosinophils from the peripheral blood is the laboratory hallmark of a severe reaction. Lymphocyte counts may fall initially, followed by lymphocytosis, but not to the same extent as with eosinophils. Leucocytosis with neutrophilia is less common. Elevations in liver enzymes occur, but rarely exceed grade 2 and usually normalize by day 30. Levels of bilirubin and alkaline phosphatase are usually unchanged. Any deviation from this pattern of liver function abnormalities should prompt investigations for an intrinsic drug effect or a coincidental illness. Proteinuria may occur. Although the laboratory changes per se have little clinical significance, they give indirect evidence of the death of microfilariae and may even indicate the speed and severity of the reaction to the event.

The factors that govern the Mazzotti reaction include the intensity of infection, the dose regimen, and the microfilaricide used. These determine the onset, evolution, reaction severity, extent of the laboratory changes, and whether the reaction is mono- or biphasic. A notable exception occurs in subjects with hyper-reactive onchodermatitis (Sowda), where severe, predominantly cutaneous adverse effects occur even with very low skin microfilarial counts.

For a given intensity of infection, the severity of the Mazzotti reaction to ivermectin is independent of dose within the range of 150 to 800 µg/kg (approximately 9 mg-48 mg). Dangerous and alarming reactions result from the simultaneous occurrence of severe reactions in multiple systems. This phenomenon is rare with ivermectin. Biphasic reactions, characterized by a marked recrudescence of cutaneous or lymph node symptoms or the development of an acute febrile polyarthritides, several days after the initial reaction, have also not been observed with ivermectin. There is no reason to believe that the Mazzotti response to moxidectin would differ radically from those due to ivermectin. However, a more rapid elimination of microfilariae may result in an earlier onset, or a more severe reaction, for a given initial infection intensity.

Severe reactions can usually be aborted by the administration of 100 to 200 mg of hydrocortisone hemisuccinate intravenously aided by supportive therapy.

The clinical events will be graded according to the National Cancer Institute common toxicity table, version 2.0, with additions specific for this protocol summarized in Attachments 5 and 6.

More frequent safety evaluations may be made if clinically indicated or at the discretion of the investigator. All adverse effects (AEs) will be recorded in the CRFs throughout the entire study.

## **18.2 Safety Assessment Methods and Dose Progression Decision**

The decision to move to the next higher dose group, will be made based on blinded review of the safety and microfilaricidal data obtained during the first 30 days post treatment of all previously enrolled cohorts.

The PI will submit a recommendation to proceed or not to proceed after a detailed examination of the blinded data. The Wyeth medical monitor, the WHO clinical monitor and the WHO Project Manager will

conduct their separate reviews. Wyeth will include a representative of its safety surveillance group in addition to the medical monitor for purposes of review. WHO may include its Clinical Coordinator or another physician in the review.

The PRT will discuss the blinded data and the recommendation to progress or not. The recommendation will be provided together with the rationale for this recommendation to CERT who have access to the randomized dose assignments and have reviewed the data in parallel with the PRT. If there is a difference of opinion within the PRT regarding the dose progression recommendation, the different recommendations and their rationale will be provided to the CERT. The CERT will provide their recommendation to the PRT.

The experts will have access to the treatment codes and will review the data initially in a blinded fashion with the option to unblind at a patient or cohort level, with special focus on the following:

- The number of possibly, probably or definitively drug related non-CNS AEs  $\geq$  grade 2 among moxidectin treated subjects.
- The number of subjects with possibly, probably or definitively drug related CNS AEs  $>$  grade 1 that are not related to the efficacy of moxidectin (i.e. not characterized by the PI as Mazzotti reactions) among moxidectin treated subjects.
- Any moxidectin treated subject with a possibly, probably or definitively drug related SAE not related to the efficacy of moxidectin (i.e. not characterized by the PI as Mazzotti reactions).

The review will take the clinical significance of the AEs in the context of the control programs into consideration.

If there is not unanimous agreement among the CERT, they will provide their differing recommendations and their rationale. If there is not unanimous agreement on proceeding to the next dosing cohort between the PRT and a majority of the CERT, the data will be discussed in a blinded fashion. If no agreement can be reached, unblinded data will be made available to the PRT for the subject(s) in question and discussed. If upon discussion of the unblinded data there is no unanimous agreement to proceed to the next higher dose group, dose progression will not occur. A more detailed description of the procedures in the dose progression monitoring plan will be reviewed and approved by the PRT and the CERT.

### **18.3 Safety Laboratory Determinations**

All clinical and laboratory evaluations that deviate from baseline values after study drug administration and are considered to be clinically significant will be repeated and followed until normalization. If normalization does not occur within 2 weeks or by day 30, the etiology will be identified, if possible, and the Wyeth medical monitor, the WHO clinical monitor, and the WHO project manager, will be notified.

## **19. EFFICACY**

### **19.1 Efficacy Variables**

Efficacy against the microfilariae will be determined by reductions from initial counts in skin and ocular microfilariae (where applicable).

#### **19.1.1 Primary**

This study will give initial indications of the efficacy of moxidectin against the microfilariae of *O. volvulus*. The primary efficacy variable will be:

- The change from baseline in the mean number of skin microfilariae per milligram of skin sampled at 4 body locations (right and left iliac crests, right and left calves) at 18 months after test article administration

#### **19.1.2 Secondary**

Secondary efficacy variables will include:

- The mean reduction from baseline, as well as the percentage of subjects with undetectable microfilariae, will be calculated by dose and severity of infection for each post treatment evaluation time point.
- The change from baseline in the mean number of skin microfilariae per milligram of skin sampled at 4 body locations (right and left iliac crests, right and left calves) at 12 months after test article administration.

- The change from baseline in the mean number of skin microfilariae per milligram of skin sampled at day 8, 1 month, 2 months, 3 months, and 6 months.
- The change from trough values to 12 months and 18 months post treatment in the mean number of skin microfilariae per milligram of skin sampled at 4 body locations (right and left iliac crests, right and left calves) to quantify the effect on the reproductive capacity of adult worms.
- The area under the curve (calculated by using the trapezoidal method through the 18 month visit)
- Ocular examination (time of maximum reduction of microfilariae and number (%) of subjects with complete clearance). The change from baseline in the mean number of ocular microfilariae measured in the anterior chamber. Living and dead microfilariae in the cornea and punctate opacities will also be counted. Retinal changes secondary to the disease will also be examined. Ocular examinations will be performed at baseline and on days 3 or 4, 7 or 8, 14 or 15, and at 1 month, 3 months, 6 months, 12 months and 18 months.
- Evidence of an effect on the viability and/or fertility of the macrofilaria will be obtained from the histologic examination of nodules excised at 18 months. Parameters to be evaluated include:
  - a. Viability (number live, moribund, dead)
  - b. Calcification (presence/absence)
  - c. Reproductive status:
    - i. Females:
      - Proportion:
        - 1. Number producing embryos up to the microfilarial stage
        - 2. Degenerated microfilariae in uterus
        - 3. Relict embryos
    - ii. Males:
      - Proportion with:
        - 1. Spermatogenesis normal or abnormal
    - iii. Other criteria:
      - Proportion of nodules with:
        - 1. Microfilariae in the capsule
        - 2. No male worms

## **19.2 Efficacy Assessment Methods**

- The maximal microfilaricidal effect on skin microfilariae will be determined by skin snips taken at day 8 and 1 month ( $\pm$  1 week).

- Nodules will be processed at 18 months for histological examination and assessed by the OCRC parasitology department (blinded to the treatment).

## **20. PHARMACOKINETIC ANALYSIS**

Blood samples for determination of moxidectin plasma concentrations will be collected within 2 hours prior to dosing (0 hr), and at 1, 2, 4, 8, 24, and 72 hours after study drug administration, on study days 8, 13, and 18 and on months 1 ( $\pm$  1 week), 2 ( $\pm$  1 week), 3 ( $\pm$  1 week), 6 ( $\pm$  1 month) and 12 ( $\pm$  1 month). PK samples will be drawn from all subjects in all cohorts with the exception of the 2nd group of 16 subjects with  $> 20$  microfilariae/mg of skin in cohorts 3, 6, and 9. Samples from subjects will be analyzed by a validated bioanalytical method.

A PK analysis will be performed using model independent methods to characterize the PK parameters of moxidectin, such as maximum plasma concentration ( $C_{max}$ ), time to reach the maximum plasma concentration ( $t_{max}$ ), area under the plasma concentration vs. time curve (AUC) and the apparent terminal elimination half-life ( $t_{1/2}$ ).

## **21. STATISTICAL ANALYSIS**

### **21.1 Statistical Methods**

This is a randomized, double-blind, active-control, dose-escalation trial comparing 3 doses of moxidectin (2, 4, and 8 mg) with ivermectin, stratified by microfilariae density (mild, moderate, severe) and gender. Subjects will be treated as in subjects for the first 18 days and as outpatients for the remainder of the 18 month study.

The primary analysis population for safety will be the modified intent-to-treat (mITT) population, which consists of all subjects who receive study medication. For efficacy, the primary analysis population will be the evaluable subject population, which is defined as all subjects who receive study medication and have baseline and 18-month microfilariae count data. An mITT sensitivity analysis will also be performed to evaluate the effect on the efficacy results of dropouts occurring before 18 months.

The primary objective of the study is to evaluate the safety of escalating moxidectin regimens. Both the incidence of clinical AEs and clinically significant laboratory test results will be used to assess safety.

The primary efficacy endpoint is the reduction from baseline in skin microfilariae at 18 months. Microfilariae count will be defined as the geometric mean of skin microfilariae/mg taken at 4 sites (iliac crests and calves).

In addition, important secondary endpoints are the reduction from baseline in skin microfilariae load at day 8, 1 month, 2 months, 3 months, 6 months and 12 months, area under the curve (calculated by using the trapezoidal method through the 18 month visit), ocular examination (time of maximum reduction of microfilariae and number (%) of subjects with complete clearance) and nodulectomy (viability and fertility of macrofilariae) at 18 months.

## **21.2 Methodology**

Initially, an overall among-group test will be performed to determine if any significant differences exist among the 4 treatment groups (2 mg, 4 mg, 8 mg moxidectin, and ivermectin). For this analysis the ivermectin control will be pooled over all nine cohorts (three dose groups). Following a significant overall result, paired comparisons (i.e., each moxidectin group versus ivermectin) will be performed to characterize the results. Prior to pooling the nine cohorts the ivermectin response for the nine cohorts will be graphically evaluated to ensure that there is no time effect on the pooled ivermectin results. For safety, moxidectin will be compared with ivermectin with respect to the incidence of AEs by using the Fisher's exact test. Laboratory data will be analyzed by using the analysis of covariance, adjusting for baseline. For efficacy, the microfilariae counts will be logarithmically transformed (Mosteller and Tukey) and analyzed by using the analysis of covariance, adjusting for baseline counts and the number of sites from which the microfilariae were taken. The latter covariate will be used to adjust for subjects who have fewer than 4 microfilarial collection sites. Factors in the model will include treatment group, covariates, level of microfilariae density (mild, moderate, severe), and gender. Also, a sensitivity analysis will be performed to examine the effect on results of second-order interactions. Data results will be summarized as adjusted geometric means. If the assumptions of normality or log-normality are not met, the data will be analyzed by using the Friedman Test, blocking on baseline skin microfilariae density and gender. In order to evaluate the robustness of the results, the microfilariae data will also be analyzed as a percent change from baseline. The proportion of subjects cured (i.e. with undetectable microfilariae) will also be evaluated.

For the analysis of microfilariae viability and fertility endpoints, proportions will be analyzed by using the Cochran-Mantel-Haenszel procedure blocking on baseline skin microfilariae density. If the overall test is significant, paired comparisons will be made comparing each moxidectin group with ivermectin.

For ocular microfilariae, time to maximum reduction will be analyzed by using the Friedman Test blocking on baseline skin microfilariae density. The proportion of subjects with complete clearance will be analyzed by the Cochran-Mantel-Haenszel procedure blocking on baseline skin microfilariae density. If the overall test is significant, paired comparisons will be made comparing each moxidectin group with ivermectin.

All tests will be performed as 2-sided tests with  $\alpha = 0.05$ .

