## 11. STUDY OBJECTIVES

### 11.1 Primary

The primary objective of this study is to determine the safety and tolerability of orally administered moxidectin in subjects with *O. volvulus* infection, as measured by the incidence of clinical AEs and clinically significant laboratory test results.

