## **17.2 Randomization**

Subjects will be assigned a randomization number by the unblinded third party pharmacist. The unblinded third party pharmacist will be supplied with 12 randomization schedules - one for each of the 3 severity levels (mild, moderate, severe) within each of the 3 dose cohorts (2 mg, 4 mg, 8 mg) and 3 additional schedules for the most severe (> 20 mf/mg of skin) subjects. Each randomization schedule will have 16 unique randomization numbers. The randomization numbers will be assigned by the unblinded third party pharmacist at the time of preparing the study medication and will be recorded on to the case report forms. Treatment groups will be blocked in groups of 4 with a 3 to 1 ratio of moxidectin to ivermectin. When the first male subject is enrolled, the assigned treatment (randomization number) will be selected from the top of the randomization list that corresponds to the subject's assigned stratum. The treatment (randomization number) for the first female subject will be selected from the bottom of the randomization list that corresponds to the subject's assigned stratum. The second male subject will be assigned the next available treatment from the top of the randomization list that corresponds to the subject's assigned stratum. The second female subject will be assigned the next available treatment from the bottom of the randomization list that corresponds to the subject's assigned stratum. Assignment to treatment group will continue in this manner until the entire cohort has been assigned to a treatment group. A new randomization schedule should be used when a new cohort is started.

At the end of the study, the randomization numbers will be used to identify the treatment group assigned to the subject.

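### The adverse-event comparison ignores the infection-density strata used for randomization; it is not biased, but it is conservative and gives up power

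*Supplement*

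**What the plan says.** Section 11.1 makes safety the primary objective, "as measured by the incidence of clinical AEs and clinically significant laboratory test results". Section 21.1 repeats it: "The primary objective of the study is to evaluate the safety of escalating moxidectin regimens".

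For the comparison of arms, Section 21.2 says: "For safety, moxidectin will be compared with ivermectin with respect to the incidence of AEs by using the Fisher's exact test". It names no stratification factor. The laboratory analysis is: "Laboratory data will be analyzed by using the analysis of covariance, adjusting for baseline".

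The design is "stratified by microfilariae density (mild, moderate, severe) and gender" (Section 21.1). Section 17.2 supplies separate schedules for each severity level within each dose: "Treatment groups will be blocked in groups of 4 with a 3 to 1 ratio of moxidectin to ivermectin". Section 18.1 states: "The factors that govern the Mazzotti reaction include the intensity of infection". The Introduction (Section 9, on route and dosage) adds that AEs after ivermectin are related to how many microfilariae are killed, and gives this as a reason for enrolling by increasing severity.

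Elsewhere in Section 21.2, worm viability and fertility and complete ocular clearance are analysed by CMH blocked on baseline skin microfilariae density. The efficacy ANCOVA includes density and gender.

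**The concern.** The strata are part of the randomization, and the protocol expects reactions to depend on them. When event rates differ between strata, a collapsed 2x2 table treats the between-stratum spread as noise. Fisher's test, already conservative, then becomes more so. In a safety comparison, a lower chance of seeing a true excess is the unhelpful direction. The question of interest, whether a dose causes more reactions than ivermectin at a given infection intensity, is also the one that a stratified analysis answers. The plan already uses the stratified method for secondary binary endpoints and gives no reason for a different approach to AEs.

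**Working it through.** **The plan's own safety figures.** Section 21.3 gives the chance of at least one AE of grade 2 or higher, which is 1 − (1 − p)^n:
- n = 12: 1 − 0.99^12 = 0.114 and 1 − 0.90^12 = 0.718.
- n = 24: 1 − 0.99^24 = 0.214 and 1 − 0.90^24 = 0.920.

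These reproduce. They concern seeing one event in a severity group. The plan gives no power for an AE comparison between arms.

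**Composition of the arms (Sections 17.2, 21.3).** At each dose, 16 mild, 16 moderate and 32 severe subjects at 3:1 give 12, 12 and 24 on moxidectin and 4, 4 and 8 on ivermectin. Ivermectin pooled over three doses is 3 × (4, 4, 8) = 12, 12 and 24. Each dose comparison is therefore 48 versus 48 with the same severity mix.

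**Why collapsing costs power.** Compare the variance of the event count in one arm: stratified, Σ n·p(1 − p), against collapsed, 48·p̄(1 − p̄). The ivermectin rates (mild/moderate/severe) are assumptions, because the documents give none.

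| Assumed rates | p̄ | Stratified | Collapsed | Ratio |
|---|---|---|---|---|
| 10/40/80% | 25.2/48 = 0.525 | 1.08 + 2.88 + 3.84 = 7.80 | 11.97 | 0.65 |
| 10/30/60% | 19.2/48 = 0.400 | 1.08 + 2.52 + 5.76 = 9.36 | 11.52 | 0.81 |
| 20/40/60% | 21.6/48 = 0.450 | 1.92 + 2.88 + 5.76 = 10.56 | 11.88 | 0.89 |
| 5/10/20% | 6.6/48 = 0.1375 | 0.57 + 1.08 + 3.84 = 5.49 | 5.69 | 0.96 |
| flat 10% | 0.100 | 4.32 | 4.32 | 1.00 |

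The smaller the ratio, the more the collapsed test overstates the noise.

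**Power and size.** The moxidectin rate in each stratum has odds equal to 3 times the ivermectin odds; 10/40/80%, for example, becomes 25/67/92%. Over all possible tables I summed the probability of p ≤ 0.05, two-sided, for three tests:
- Fisher on the totals.
- The exact conditional stratified test, which convolves the three hypergeometric distributions.
- CMH without continuity correction: (ΣA − ΣE)²/ΣV against 3.84, with E = n_t·m/N and V = n_t·n_c·m(N − m)/[N²(N − 1)].

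| Assumed rates | Fisher | Exact stratified | CMH | Fisher size at OR 1 |
|---|---|---|---|---|
| 10/40/80% | 25.4% | 44.3% | 54.2% | 0.8% |
| 10/30/60% | 47.3% | 57.0% | 65.2% | 1.5% |
| 20/40/60% | 56.4% | 61.6% | 69.1% | 2.2% |
| 5/10/20% | 44.2% | 46.5% | 56.0% | 1.9% |
| flat 10% | 38.6% | 39.2% | 49.6% | 1.7% |

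Exact against exact, stratification gains 18.9, 9.7, 5.2, 2.3 and 0.6 points. The further step to asymptotic CMH (8 to 10 points) comes from dropping the conservatism of exact tests, not from stratifying. The size of CMH is 4.9 to 5.2% in these settings.

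At an odds ratio of 2, no setting reaches more than 37% with any of the three tests, even at a flat 30%. There the sample size is the main limit.

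**The case against.** **No bias.** A reader might infer that true AE differences will be missed, or that the unstratified result is confounded by severity. The documents support neither. The severity mix is identical in the arms by design, so imbalance gives no false reassurance. What is lost is power, and the amount depends on a severity gradient that the documents never quantify. This part of the objection stands in full.

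**The largest contrast is not typical.** Fisher at 25% against CMH at 54% needs an eightfold gradient and also mixes two effects. The illustrative rates in Section 21.3 are 1% and 10%; for uncommon events stratification alone adds about 2 points or less in the settings above. This also stands.

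**Laboratory results.** A reader might infer that the laboratory half of the objective has no incidence analysis, because only an ANCOVA is named. That goes too far. Section 23.1 counts laboratory observations as AEs, Section 23.3 has clinically relevant abnormal values reported by the AE/SAE process, and Attachment 5 grades them. They can already enter the AE comparison. Nor does the plan say that laboratory values are averaged over visits, so an eosinophil fall followed by a rise need not cancel out.

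**Other safeguards.** Dose progression (Section 18.2) rests on direct review of events, with the option to unblind, and not on this test. No separate analysis plan is shown, so missing summaries by stratum are no fault. However, the test itself is stated in Section 21.2, and no reason is given for setting aside the strata there.

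**Conclusion.** The point holds as a matter of efficiency and internal consistency. The AE comparison leaves out a randomization factor that the protocol expects to drive reactions and that the same section uses for other proportions. The comparison remains valid and unbiased, but it is conservative: Fisher's true size is about 0.8 to 2.2% in the five settings, against a nominal 5%. At an odds ratio of 3, an exact stratified test gains between almost nothing (no gradient) and about 19 points (steep gradient). With no gradient it costs essentially nothing.

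These figures rest on assumed event rates, a common odds ratio across strata, full enrolment at 12/12/24 per arm, and pooling of ivermectin over cohorts as Section 21.2 plans. The change is worth making before unblinding. It does not call the safety conclusions into doubt.

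**What to change.** In Section 21.2, replace Fisher's test for AE incidence with the CMH procedure blocked on baseline skin microfilariae density, using the exact conditional version when events are sparse. For each moxidectin dose versus pooled ivermectin, report a density-stratified odds ratio or risk difference with a 95% CI. State that clinically significant graded laboratory abnormalities, which already count as AEs, go through the same stratified comparison, and keep the ANCOVA of laboratory values alongside.

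The cost is a few sentences and a little programming. The strata, the grading tables and the CMH method are already in the plan, and no extra data are needed.

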### **21.3 Sample Size and Power**

For the mild and moderate severity levels in each dose group, 16 subjects will be randomly assigned in a 3:1 ratio to either moxidectin or ivermectin, for the severe level in each dose group 32 subjects will be randomly assigned to treatment using the same ratio. The probability of detecting at least 1 AE of ~~NCI~~ grade 2 or higher among 12 moxidectin-treated subjects will be 0.114 and 0.718 when the true rates are 1% and 10%, respectively. The probability of detecting at least 1 AE of ~~NCI~~ grade 2 or higher among 24 moxidectin-treated subjects will be 0.214 and 0.92 when the true rates are 1% and 10%, respectively.

For efficacy, given that the subjects in the three severity levels within a moxidectin dose group can be pooled and that all ivermectin subjects can be pooled, there will be 48 subjects per moxidectin dose group and 48 subjects in the pooled ivermectin treatment group. With 48 subjects per treatment group there is 78.3% power to detect a statistically significant difference between a response (% of baseline microfilariae) of approximately 0.1% (moxidectin) and 20% (ivermectin) at 18 months after treatment.

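### The per-dose adverse-event comparison with ivermectin is conditional on a significant four-group test and carries no effect estimate or interval, so a doubling of less common events at one dose would more likely than not be non-significant

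*Supplement*

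**What the plan says.** Section 21.1 of the amended protocol states: "The primary objective of the study is to evaluate the safety of escalating moxidectin regimens". It names two measures, the incidence of clinical AEs and clinically significant laboratory results. The safety set is everyone treated: "The primary analysis population for safety will be the modified intent-to-treat (mITT) population, which consists of all subjects who receive study medication".

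Section 21.2 sets the order of testing before it turns to safety or efficacy. First, "Initially, an overall among-group test will be performed to determine if any significant differences exist among the 4 treatment groups", with the ivermectin subjects of all cohorts pooled. Then, "Following a significant overall result, paired comparisons (i.e., each moxidectin group versus ivermectin) will be performed to characterize the results". The safety sentence follows: "For safety, moxidectin will be compared with ivermectin with respect to the incidence of AEs by using the Fisher's exact test". It does not say whether this is dose by dose or all moxidectin together, and it does not lift the preceding condition. Laboratory data get an analysis of covariance adjusted for baseline. On error rates: "All tests will be performed as 2-sided tests with" α = 0.05.

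Section 21.3 gives the group sizes in its efficacy paragraph: "there will be 48 subjects per moxidectin dose group and 48 subjects in the pooled ivermectin treatment group". Its only safety sizing is the chance of seeing at least one AE of grade 2 or higher among 12 or 24 moxidectin subjects. Nowhere does section 21 give a risk difference, an interval or a target difference for AEs.

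**The concern.** When the question is safety, the costly error is the missed difference, and a test at 0.05 does not control it. The protocol expects any divergence to run in one direction: section 18.1 notes that faster killing of microfilariae could bring an earlier or more severe reaction.

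Followed literally, 21.2 can end the AE analysis at a non-significant four-group test, with no dose ever contrasted with ivermectin. Even when the contrast is made, the named output is a p-value. At 48 per group a large p-value is compatible with a sizeable excess at one dose, and the planned output would not show how large.

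**Working it through.** **Inputs.** Per dose, 12 + 12 + 24 = 48 moxidectin subjects. Ivermectin, (4 + 4 + 8) × 3 = 48. All treated subjects count, so nothing is deducted for dropout. Tests are two-sided at 0.05. The ivermectin AE incidence in this population is not given, so I assume a range of 5% to 35%. Two reference points in the documents are the illustrative rate of 10% in 21.3 and the 35% (headache) and 29% (infection) quoted in section 22 from healthy volunteers.

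**The plan's own safety figures.** P(at least one event) = 1 − (1 − p)^n. For n = 12: 0.1136 at 1% and 0.7176 at 10%. For n = 24: 0.2143 and 0.9202. These match the stated 0.114, 0.718, 0.214 and 0.92. They describe a single arm and do not bear on the comparison with ivermectin.

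**Power of the comparison.** Scenario: one dose has twice the ivermectin rate and the other two doses equal ivermectin. Fisher alone is the sum, over all pairs of counts from 48 and 48, of the binomial probabilities of pairs where the two-sided p ≤ 0.05 and the dose has more events. The last column also requires the four-group test to be significant. The plan does not name that test; I used Pearson chi-square with 3 degrees of freedom, enumerated exactly.

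| Ivermectin → one dose | Fisher alone | Fisher and overall test |
|---|---|---|
| 5% → 10% | 5.8% | 5.0% |
| 10% → 20% | 18.2% | 15.5% |
| 15% → 30% | 33.4% | 29.1% |
| 20% → 40% | 49.0% | 44.5% |
| 22% → 44% | 55.0% | 50.8% |
| 25% → 50% | 64.3% | 61.1% |
| 30% → 60% | 80.0% | 78.0% |
| 35% → 70% | 91.4% | 90.4% |

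The 50% line is crossed just above 20% for Fisher alone (50.5% at 20.5%) and between 21.5% (49.2%) and 22% (50.8%) with the overall test. The gap between the columns is about 1 to 5 points, so most of the shortfall comes from 48 per group.

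**If the Fisher sentence means all doses pooled (144 v 48).** A doubling at one dose alone would be significant about 6% of the time from 10%, 13% from 20% and 28% from 35%.

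**What an interval would add.** With 5/48 on ivermectin and 10/48 on one dose, Fisher gives p = 0.26. The difference is 10/48 − 5/48 = 10.4 points, with a 95% interval (Newcombe score method) from −4.4 to +25.1. With equal counts of 5/48 or 10/48 in both arms, the upper limit is still about +13 or +16 points.

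**The case against.** The other side has several good points.

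- **A doubling is not always missed.** A reader might infer that a doubling at one dose is more likely than not to go undetected whatever the event. That is wrong above about 22%. Section 18.1 lists pruritus, rash, headache, myalgia and fever as common reactions, so low incidence cannot be presumed for the main ones. This stands and limits the point to less common events.
- **Non-significance is not declared to mean comparable safety.** A reader might infer that it would be read that way. No passage says so, and no non-inferiority claim is planned. This stands too.
- **Escalation does not depend on this test.** Sections 10.1 and 18.2 rest dose progression on review by the project team and independent clinical experts, with an option to unblind. That is true, but the review uses 30-day data and is not the end-of-study comparison with ivermectin.
- **Laboratory data have their own analysis.** Fisher is therefore the only planned comparison of AE incidence, not the only safety inference.
- **The condition is read across from a general rule.** The Fisher sentence does not repeat it. But the rule opens the section and exempts nothing.
- **Intervals are often left to an analysis plan, and none is shown.** Their absence alone would be a weak complaint, and differences can be computed from the counts by arm. The order of testing and the choice of test, however, are written here, and a later plan would have to depart from them.

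**Conclusion.** The point holds in a limited form. As written, 21.2 can withhold the per-dose AE contrast on which the primary objective depends, and it names a p-value as the only result of that contrast. For AEs with an ivermectin incidence of about 20% or less, a doubling at one dose would more likely than not be non-significant: at 10% it is missed about 82% of the time by Fisher alone (100 − 18.2) and about 84% with the overall test (100 − 15.5). At 30% or 35% it would usually be found.

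This rests on 48 v 48, a single affected dose, a chi-square overall test and an assumed ivermectin incidence. It does not show that the conditional step is the main cause of low power, since removing it recovers only a few points. Its harm is that the estimate may never be presented.

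**What to change.** In section 21.2, state that AE incidence is compared for each moxidectin dose with pooled ivermectin regardless of the overall test. Report each difference in incidence with a two-sided 95% score interval, and keep the Fisher p-value as descriptive. Naming the comparison dose by dose also settles whether the Fisher sentence means separate or pooled doses.

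Add one sentence saying that lack of significance will not be taken as evidence of comparable safety. No non-inferiority margin is needed.

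The cost is a few lines of text and one extra column in the AE tables, with no additional subjects, visits or data. The intervals will be wide and will show it openly. The change does not raise power, which the group size fixes.
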